### Gabapentin

Gabapentin is approved for the treatment of epilepsy and neuropathic pain. The definite mechanism of action by which gabapentin exerts anti-convulsant and analgetic effects has not been fully clarified. Oral gabapentin will be given at a dose of 3 × 300 mg/day in week 1, 3 × 600 mg/day in week 2, 3 × 900 mg/day in week 3 and 3 × 1200 mg/day from week 4 onwards. The most common adverse events related to gabapentin include neurological symptoms, e.g. ataxia, somnolence, dizziness, vertigo, tremor, diplopia, amblyopia and nystagmus. Dosing will be permanently discontinued if DRESS syndrome attributed to gabapentin occurs.

### Sulfasalazine

Sulfasalazine is approved for the treatment of ulcerative colitis and rheumatoid arthritis. Oral sulfasalazine will be given at a dose of 3 × 500 mg/day in week 1, 3 × 1000 mg/day in week 2 and 3 × 1500 mg/day from week 3 on. Dosing will be reduced if hematologic, liver or renal toxicity occurs and will be permanently discontinued if Lyell syndrome, Stevens Johnson syndrome or DRESS syndrome occurs.

### Memantine

Memantine is approved for the treatment of Alzheimer’s disease. Oral memantine will be given at a dose of 1 × 5 mg/day in week 1, 1 × 10 mg/day in week 2, 1 × 15 mg/day in week 3 and 1 × 20 mg/day from week 4 onwards). Higher grade toxicity from memantine is overall rare.

### Radiotherapy

Patients will receive radiotherapy in daily fractions of 1.8 - 2 Gy given 5 days per week over 6-7 weeks, for a total dose of 60 Gy delivered in 30 - 33 fractions. Radiotherapy will be administered concomitantly with temozolomide and in the experimental arm also with the investigated drugs. Target volume delineation will be based on postoperative MRI scans (minimum: T1 native and T1 + Gadolinium, T2/FLAIR; axial orientation) obtained for treatment planning taking pre-operative MRI into consideration as well. Every effort is made to deliver the full dose to all patients. Up to 7 days of treatment interruption are permitted for any reason.

### Temozolomide

Temozolomide will be administered during radiotherapy at a dose of 75 mg/m^2^ daily at 7 days per week. This is followed by maintenance therapy with up to 6 cycles temozolomide at 150 to 200 mg/m^2^ for 5 consecutive days every 4 weeks, beginning 4 weeks after the end of radiotherapy [3]. The most common expected toxicity is myelosuppression. If adverse events persist, treatment will be delayed by 1 week for up to 4 consecutive weeks, after which temozolomide will be discontinued, if adverse events have not resolved to ≤ grade 1.

### Statistical considerations

We considered an increase of the progression-free survival rate at 6 months (PFS-6) rate by 20% a clinically meaningful result that would warrant further exploration in a phase III clinical trial (assuming 50% survival rate following chemoradiotherapy alone and 70% with chemoradiotherapy plus gabapentin, sulfasalazine and memantine). At a power of 80% and a one-sided significance level of 10%, allowing a 10% drop-out rate, 120 patients need to be recruited (60 patients per arm) to detect this difference. The primary outcome will be assessed using a one-sided comparison of the PFS-6 proportion of patients in the two treatment arms at significance level 10% and a 90% confidence interval for the risk difference. Subgroup analyses will be based on two-sided interaction tests at a significance level 5%. The 8 subgroup analyses will not be adjusted for multiplicity and potential findings will be interpreted exploratively.

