**Methods/design:**

GLUGLIO is a 1:1 randomized phase Ib/II, parallel-group, open-label, multicenter trial of gabapentin, sulfasalazine, memantine and chemoradiotherapy (Arm A) versus chemoradiotherapy alone (Arm B) in patients with newly diagnosed glioblastoma. Planned accrual is 120 patients. The primary endpoint is progression-free survival at 6 months. Secondary endpoints include overall and seizure-free survival, quality of life of patients and caregivers, symptom burden and cognitive functioning. Glutamate levels will be assessed longitudinally by magnetic resonance spectroscopy. Other outcomes of interest include imaging response rate, neuronal hyperexcitability determined by longitudinal electroencephalography, Karnofsky performance status as a global measure of overall performance, anticonvulsant drug use and steroid use. Tumor tissue and blood will be collected for translational research. Subgroup survival analyses by baseline parameters include segregation by age, extent of resection, Karnofsky performance status, O^6^-methylguanine DNA methyltransferase *(MGMT)* promotor methylation status, steroid intake, presence or absence of seizures, tumor volume and glutamate levels determined by MR spectroscopy. The trial is currently recruiting in seven centers in Switzerland.

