### Trial design

This study is an open-label, randomized, multicenter, phase Ib/II clinical trial. Following informed consent, patients who meet eligibility criteria will be randomly allocated in a 1:1 fashion to receive either a triple glutamate-targeted treatment with gabapentin, sulfasalazine and memantine plus chemoradiotherapy with temozolomide or chemoradiotherapy alone (Fig. 1). A total of 120 patients will be randomized with 60 participants in each study arm. The allocation sequence will be generated in advance using stratified block randomization with varying block sizes. Randomization will be stratified by extent of resection (gross total versus subtotal resection or biopsy). Post hoc central neuropathology review will be conducted for quality assurance. Randomized patients will enter the treatment phase and will be followed-up until death. Tumor progression will be assessed by contrast-enhanced magnetic resonance imaging every 3 months. An epileptic seizure assessment questionnaire will be filled in at every study visit and routine electroencephalography will be performed every 3 months to assess epileptic seizure control and neuronal hyperexcitability. Data bank closure will be 6 months after the last participant was randomized.

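### The primary PFS-6 comparison as stated uses neither the randomisation stratum nor MGMT status; prespecified adjustment would be a cheap, modest improvement to a valid test

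*Protocol article*

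**What the plan says.** All references are to the protocol article.

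- **Statistical considerations:** the primary outcome is assessed by a "one-sided comparison of the PFS-6 proportion of patients in the two treatment arms", at a one-sided 10% level, with a 90% confidence interval for the risk difference. No stratification factor or covariate is named. The comparison is not labelled unadjusted either.
- **Trial design:** "Randomization will be stratified by extent of resection (gross total versus subtotal resection or biopsy"). No other stratification factor is named.
- **Abstract, Methods/design:** the baseline parameters for subgroup survival analyses include age, extent of resection, Karnofsky status and MGMT "promotor methylation status, steroid intake, presence or absence of seizures, tumor volume and glutamate levels determined by MR spectroscopy". Statistical considerations then says that subgroups are examined by interaction tests.
- **Sample size (Statistical considerations):** "At a power of 80% and a one-sided significance level of 10%, allowing a 10% drop-out rate, 120 patients need to be recruited", with the rates given as "assuming 50% survival rate following chemoradiotherapy alone and 70% with chemoradiotherapy plus gabapentin, sulfasalazine and memantine".

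In the article, therefore, extent of resection has a role in the randomisation and in the subgroups, MGMT has a role in the subgroups only, and neither has a stated role in the primary test.

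**The concern.** When randomisation is stratified by a factor, the usual practice is to carry that factor into the primary analysis. When another baseline factor expected to be prognostic is collected anyway, naming it in advance as a covariate can sharpen the estimate and take account of whatever imbalance chance produces. The article does neither in its primary analysis.

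The trial is small and feeds a decision about phase III. Its Discussion calls the sample size a major limitation and says that an absent signal would count strongly against glutamate-targeted treatment. At stake are a few points of power and how far one trial's result can be moved by the MGMT mix that its arms happen to receive. Adding MGMT after an imbalance has been seen would be less credible than naming it beforehand.

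**Working it through.** **1. Reproduce the stated sample size.** Inputs from Statistical considerations: 50% v 70%, one-sided 10% (z = 1.2816), power 80% (z = 0.8416), 10% drop-out. The pooled two-proportion formula without continuity correction gives

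n = [1.2816·√(2·0.6·0.4) + 0.8416·√(0.5·0.5 + 0.7·0.3)]² / 0.20² = (0.8879 + 0.5708)² / 0.04 = 53.2, so 54 per arm.

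54 / 0.9 = 60 per arm, 120 in all. This matches the article exactly, so the trial was sized for an unadjusted comparison.

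**2. Is the unadjusted test sound?** Its exact one-sided type I error at a common rate of 50% is 10.5% at 54 per arm and 10.0% at 60. Its exact power is 80.7% and 85.0%. With prognostic factors present and blocks balanced within resection strata, its simulated type I error at 54 per arm was 10.0% to 10.5% (40,000 trials per scenario). Ignoring the stratum makes the standard error, if anything, slightly too large. With a 20-point resection effect, the between-stratum share of the variance is 0.2²·0.25 / 0.24 = 4.2%, or about 2% of the standard error.

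**3. What adjustment would gain.** The documents give no prevalence or prognostic effect, so these are assumptions: 50% gross total resection, 40% MGMT-methylated, and additive effects g (resection) and m (MGMT) on PFS-6. The between-stratum variance is v = 0.25g² + 0.24m². Adjusted power is approximately

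Φ{[0.20 − 1.2816·√(2(0.24 − v)/n)] / √((0.46 − 2v)/n)}.

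Example with g = 0.20, m = 0.30, n = 54: v = 0.010 + 0.0216 = 0.0316. Power = Φ[(0.20 − 1.2816·0.0879)/0.0857] = Φ(1.02) = 84.6%. With v = 0 it is 80.5%.

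| g / m (points) | Formula, 54 per arm: none / resection / both | Simulated, 54 per arm: unadjusted → both | Simulated, 60 per arm: unadjusted → both |
|---|---|---|---|
| 0 / 0 | 80.5 / 80.5 / 80.5 | 80.9 → 80.2 | 85.0 → 83.3 |
| 10 / 10 | 80.5 / 80.8 / 81.1 | 80.7 → 80.6 | 85.3 → 83.8 |
| 15 / 20 | 80.5 / 81.2 / 82.4 | 80.8 → 82.1 | 85.4 → 85.1 |
| 20 / 20 | 80.5 / 81.7 / 83.0 | 81.2 → 82.7 | 85.5 → 85.7 |
| 20 / 30 | 80.5 / 81.7 / 84.6 | 81.2 → 84.5 | 85.7 → 87.3 |

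The simulations used a Mantel-Haenszel test over four strata. A separate set of 6,000 trials per scenario at 54 per arm, with linear standardisation, gave gains of 1.3 to 2.7 points for MGMT effects of 20 to 30 and resection effects of 15 to 20. Resection alone is worth about 0 to 1 point. At 60 per arm the unadjusted test does better than its normal approximation (85.0% exact v 83.5%), which helps to explain why adjustment can lose there.

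**4. MGMT imbalance.** With 40% methylated and 60 per arm, the standard deviation of the between-arm difference is √(2·0.24/60) = 8.9 points. P(difference above 10 points) = 2[1 − Φ(0.10/0.0894)] = 26%. At 54 per arm it is 29%. A 10-point imbalance moves the unadjusted difference by 0.10·m, which is 2 to 3 points for m = 20 to 30. The target is 20 points and the standard error is √(0.46/54) = 9.2 points.

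**5. What that means for one trial, at 54 per arm.** The test rejects above about 1.2816·√(0.48/54) = 12.1 points.

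- Given a 10-point imbalance in favour of Arm A and no treatment effect, the chance of rejection is P[Z > (12.1 − 2)/9.2] to P[Z > (12.1 − 3)/9.0], about 14% to 16%.
- Given the same imbalance against Arm A and the planned effect, power is Φ[(18 − 12.1)/9.0] to Φ[(17 − 12.1)/8.8], about 74% to 71%.

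These figures are conditional on the imbalance. Over all randomisations the level stays near 10%.

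**The case against.** The strongest reply is that the article never says the comparison is unadjusted. A Mantel-Haenszel risk difference stratified by resection would also fit the sentence. Covariates are commonly left to the full protocol or analysis plan, which are not shown, and trials are often sized without covariates and then analysed with them. This stands to the extent that the point can only concern the analysis as the article states it. If the analysis plan already adjusts, citing it closes the matter.

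Four stronger readings are tempting, and the documents do not support them:

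- **The test or its standard error is wrong.** Type I error is close to nominal and the stated power is met.
- **The design leaves the comparison unprotected.** Blocks within resection strata already largely balance that factor, and randomisation protects MGMT in expectation. The imbalance argument therefore applies to MGMT and not to the stratum.
- **An MGMT imbalance is bias.** It is random error that the standard error already covers.
- **The precision is free.** The gain depends on prognostic strengths that the article does not give, and it can be slightly negative.

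The choice of MGMT over the other listed baseline factors is also this review's proposal and not something that the article establishes.

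**Conclusion.** The point holds as a suggestion for improvement. As stated, the primary analysis uses neither the stratum nor MGMT, and the sample size matches an unadjusted test. That test is valid and adequately powered, so nothing in the article is in error here.

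Under the assumed ranges, adjusting for both factors changes power by about 0 to +4 points at 54 evaluable per arm. At 60 per arm the simulated change runs from about −2 points with weak factors to about +1.6 with the strongest ones considered. The clearer benefit is having a rule fixed in advance for an MGMT imbalance above 10 points, which has about a 26% chance at 40% prevalence and is worth 2 to 3 points on the difference per 10 points of imbalance if MGMT shifts PFS-6 by 20 to 30 points. All of these sizes rest on assumed prevalences and effects.

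**What to change.** Unless the analysis plan already does so, state the primary estimate as a risk difference stratified by extent of resection and MGMT status (Mantel-Haenszel), or as a marginal risk difference standardised from a model with arm and those two factors. Treat unknown MGMT as its own category. Keep the one-sided 10% level and the 90% confidence interval, and report the unadjusted comparison as a sensitivity analysis. Because the trial is open-label, fix this before outcomes are compared by arm.

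The cost is a few sentences and a little programming. No patients are added, and the planned subgroup analyses already require both factors. The downside is the possible loss of up to about 2 points of power if both factors prove weak. The unknown-MGMT category was not part of the calculations. It makes up to six cells, so if some are sparse the standardised version is the easier one to apply.

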## Discussion

The recent discovery of glutamatergic neuroglial synapses between peritumoral neurons and glioma cells has sparked cancer neuroscience as a rapidly evolving research field [8, 35]. Several pre-clinical studies suggest that pharmacologic interference with these synapses may inhibit glioma growth and invasion [10, 11, 22, 35]. Hyperexcitability of neuronal networks and tumor-associated epilepsy are deemed drivers of neuroglial signaling [22, 36]. Finally, non-synaptic secretion of glutamate into the tumor microenvironment by glioblastoma cells may likewise contribute to hyperexcitability and glioblastoma progression [20, 37]. The randomized GLUGLIO trial explores the efficacy of a triple anti-glutamatergic combination of gabapentin, sulfasalazine and memantine to address whether glutamate may be exploited as a therapeutic lever.

Gabapentin reduces glutamate synthesis through inhibition of BCAT-1 [17] and, through the inhibition of thrombospondin-1 receptor α2δ-1, has been found recently to reduce functional connectivity of glioma and neuronal networks by inhibiting synaptogenesis and thus reducing tumor cell proliferation [22]. Moreover, the anti-convulsant effect of gabapentin alone may be beneficial to patients since a contribution of epilepsy to glioblastoma progression has been suggested by several pre-clinical and clinical studies [16, 22, 36], and long-term electroencephalography suggests that sub-clinical epileptic activity is common [15].

Along the same lines, a reduction in tumor-associated epilepsy has also been demonstrated for the inhibitor of the glutamate-cystine antiporter system x_c_ by sulfasalazine [37, 38]. A decrease of peritumoral glutamate after a single sulfasalazine administration has been documented in glioblastoma patients utilizing magnetic resonance spectroscopy [18].

Memantine may inhibit NMDA receptor-dependent synapse formation between neurons and tumor cells, interfering with similar processes as in long-term potentiation during physiologic memory formation [39] and as has been demonstrated in synapse formation between neurons and brain metastatic cancer cells [26]. Moreover, neuroprotective effects of NMDA receptor inhibition may enhance neurocognitive function, similar to the indication of memantine in the treatment of Alzheimer’s dementia [40].

Of the investigational medical products tested in the GLUGLIO trial, only two small, uncontrolled clinical studies have thus far sought to explore the efficacy of sulfasalazine and memantine, respectively: One study of monotherapy with sulfasalazine in glioblastoma patients with advanced disease has been terminated for lack of efficiency following the inclusion of 8 patients [41]. In an early phase clinical trial, memantine in combination with temozolomide with or without mefloquin and metformin was administered to patients with newly diagnosed glioblastoma and memantine was overall well tolerated [42]. However, the exploratory efficacy results of this trial are difficult to interpret, because there was no standard of care control arm, sample size per treatment arm was small and survival was not reported by treatment arm or excluding patients with isocitrate dehydrogenase-mutant astrocytomas.

Two ongoing phase I/II clinical trials seek to explore pharmacological interference with neural circuits and tumor cell networks in glioblastoma. The first trial conducted by the Neuro-Oncology Working Group of the German Cancer Society investigates meclofenamate as a means to disrupt gap junctions within tumor-microtube networks in recurrent glioblastoma, the primary endpoint being safety and efficacy measured by incidence of dose-limiting toxicities and progression-free survival, respectively (EudraCT 2021-000708-39). The second trial evaluates biological effects of perampanel, a non-competitive antagonist of AMPA-receptors, on neuron-tumor interactions in a pre-surgery setting (EudraCT 2023-503938-52). Another report of ten glioma patients treated with perampanel for intractable epilepsy found at best minor effects on tumor growth based on MR images [43]. However, the small cohort size and inclusion of various glioma entities limits the interpretability of this study with respect to anti-tumor efficacy. Other than the GLUGLIO trial, no randomized clinical trials or uncontrolled studies with efficacy endpoints addressing the interplay of neuronal networks and glioblastoma cells have been registered by 11/2023.

Whether or not epilepsy is causally related to survival of glioblastoma patients is not known. In fact, epilepsy has been proposed as an indicator of longer survival of glioblastoma patients [44], albeit retrospective analysis of survival associations with epilepsy are difficult to assess for several reasons, e.g. glioblastomas becoming symptomatic due to epilepsy as compared to such becoming symptomatic from other neurological deficits may be diagnosed earlier during the disease course, and rates of complete resection may be higher due to cortical tumor location and smaller tumor size [45]. One retrospective study therefore employed time-dependent multivariate analyses to analyze associations of epilepsy with survival of glioblastoma patients and supported the notion of unfavorable effects of epilepsy [16]. Finally, anticonvulsant therapy with valproic acid or levetiracetam was not associated with overall survival of glioblastoma patients in a post hoc analysis of a large merged cohort derived from different phase 3 clinical trials [46], but such analyses have limitations since only drug use at distinct timepoints could be analyzed and extent of drug exposure therefore remains uncertain.

The GLUGLIO trial addresses some of these issues, since pre-specified subgroup analyses, albeit with low power, try to address survival separately among patients with or without epilepsy will enhance our understanding of whether or not anti-convulsant therapy may indeed be beneficial for glioblastoma patients who do not suffer from clinically apparent epilepsy. The secondary objective of the GLUGLIO trial to explore epileptic activity and the conduct of serial EEG recordings will also help to better understand the postulated interplay between epilepsy and tumor progression.

A major limitation of the GLUGLIO trial is the small sample size, requiring one-sided hypothesis testing and setting the significance level to 10%. Small sample size will moreover limit the sensitivity of pre-defined subgroup survival analyses and of putative signal seeking post hoc analyses. Moreover, if efficacy of the addition of triple anti-glutamatergic therapy will indeed be observed in this trial, the combination approach precludes the definite assignment of efficacy to either of the individual drugs, thus compromising the design of a putative phase III follow-up trial. Additional pre-clinical studies in relevant tumor models will therefore be required. However, the rationale for the combination approach over testing a single drug was that combined targeting of glutamate synthesis (gabapentin), secretion (sulfasalazine) and signaling (memantine) may have additive effects, and that the lack of an efficacy signal would in reverse lend strong rationale against glutamate-targeted treatment approaches in the future.

The GLUGLIO trial is currently ongoing and first results are expected by the end of 2026.

## Data Availability

No datasets were generated or analysed during the current study.

## Abbreviations

BCAT-1: Branched chain amino acid transaminase-1
DRESS: Drug rash with eosinophilia and systemic symptoms
ESAQ: Epileptic seizure assessment questionnaire
Gy: Gray
NMDA: N-methyl-D-aspartate
PFS: Progression-free survival
RANO: Response Assessment in Neuro-Oncology
